
### Randomisation procedures

An equal number of participants in the intervention and control group will be determined for each study centre. For this purpose, all eligible participants draw a lot with either INT or CTR after the baseline assessment. The number of lots for INT and CTR is equal and limited. Drawn lots are not returned to the lottery pot until all lots have been drawn. The examiners of the centres have no influence on the allocation to the groups, a change between groups is not possible.

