#### Silver Index (SI)

Inputs into the SI are age, number of falls in the last 12 months, and the outcomes of following 8 tests for gait, balance, and rising from a chair (for detailed test procedures, and the calculation of the SI, see [35]:

Gait:
1. a 6-m walk test is used for determining gait speed;

Balance control is tested while the participant is standing on a force platform (foot platform) under the following conditions:2. quiet standing with eyes open on static foot platform (30 s);3. quiet standing with eyes closed on static foot platform (30 s);4. standing with eyes open on an unstable foot platform (responding to the participant’s postural oscillations; 30 s);5. standing with eyes open while the foot platform is moving along a default trajectory (30 s);6. reactive balance: standing with eyes open while the foot platform implements specific perturbations (with impulses of 6 degrees in random directions and in random order;7. limits of stability test: the person is instructed to move his/her body’s centre of mass as far as possible in anterior–posterior and medio-lateral directions without needing to step to maintain balance;

Muscle function (lower extremities):8. the Five Times Sit to Stand Test (FTSST) is used as a functional test for lower extremity muscle function.

Based on these tests, the SI indicating fall risk was calculated [35]. SI ranges between 0 and 100%, a score higher than 40% is considered to indicate an increased fall risk and is used as inclusion criteria for participation in this study. In addition to the overall SI, the hunova robot compares the results of seven dimensions (static balance, dynamic balance, reactive balance, limits of stability, gait speed, sensory integration, and sit to stand) to a reference sample of the same age. Based on this comparison, each dimension is defined as normal (on average) meaning no deficit or having a performance below average resulting in a yellow (poor performance), orange (very poor performance), or red deficit (very very poor performance) for this dimension. The dimensions (and deficits) are visualised in a radar plot (see Fig. 3). These dimensions and deficits are relevant for the planning of the training sessions within the intervention (see ‘intervention’).

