### Statistical analyses

#### A-priori estimation of sample size

Based on Sherrington and colleagues [10], it is assumed that the intervention will reduce the number of falls by 23% in comparison to the control group. Based on recommendations by Robertson [47], a binominal regression analysis was used to estimate the required sample size. Using G*Power [48, 49], a regression analysis with group (INT/CTR) as independent variable and number of falls as dependent variable, and -23% as the assumed reduction of falls, yielded a required total sample size of 181 persons. Assuming that the study will have an overall dropout rate of 30% [10], a total number of 235 participants to be included in the study is estimated.

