#### Planned statistical evaluation of outcomes

An analysis of primary outcomes (i.e., number of falls and number of persons who have fallen) will be based on binomial regression analyses with demographic variables, physical activity, and health parameters as covariates. Analyses of secondary outcomes (SI and TUG) will be based on 2 × 4 ANOVA / ANCOVA with groups (INT/CTR) and time of assessment (T_0_, T_1_, T_2_ and T_3_) as factors, and will consider demographic variables, physical activity, and health parameters as co-variates. Significant main or interaction effects will be investigated further using Bonferroni post-hoc-tests. The significance level is set to *p* < 0.05.

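### SI and TUG are analysed with the pre-allocation T0 value as an outcome level: the group main effect is diluted to 0.75 of a constant effect and no treatment contrast is named

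*Protocol article*

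**What the plan says.** The section on planned statistical evaluation of outcomes fixes the model for the two secondary outcomes: "Analyses of secondary outcomes (SI and TUG) will be based on 2 × 4 ANOVA / ANCOVA with groups (INT/CTR"). The second factor is the visit, and all four assessments are levels of it, T0 included. The analysis "will consider demographic variables, physical activity, and health parameters as co-variates"; the T0 value of SI or TUG is not named. On interpretation it says: "Significant main or interaction effects will be investigated further using Bonferroni post-hoc-tests". The level is 0.05. No effect is singled out as the test of treatment.

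Under Randomisation procedures, eligible participants "draw a lot with either INT or CTR after the baseline assessment", so T0 precedes allocation. Under Silver Index, a score above 40% at T0 is required for entry, and the score's ingredients are given as follows: "Inputs into the SI are age, number of falls in the last 12 months", plus eight performance tests.

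**The concern.** A value taken before allocation cannot carry a treatment effect. Used as one of four outcome levels, it pulls the group main effect towards zero. It also no longer serves as a covariate, where it would remove between-person variance. The word ANCOVA does not repair this, because the listed covariates do not include the T0 value.

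The follow-up rule treats three omnibus effects alike. Only comparisons between the groups rest on randomisation. The time main effect does not, and because entry selects on SI above 40%, regression to the mean makes a fall in SI likely in both arms. At stake is the protocol's second hypothesis, that the intervention reduces fall risk: it is tested less sharply than the collected data allow, with the deciding contrast left open.

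**Working it through.** **Inputs from the protocol.** Four visits, with T0 before allocation; 1:1 allocation; 235 to be included; 30% dropout ("Assuming that the study will have an overall dropout rate of 30"%); level 0.05.

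**Plan's own figure.** 181 × 1.30 = 235.3, which reproduces the 235. With 30% lost, 235 × 0.70 = 164.5, so about 164 people (82 per arm) have all four visits. The same 164 are used below for every test, so that the tests differ only in their form.

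**Assumptions, not in the documents.** Compound symmetry with correlation ρ; unit SD; true group difference 0 at T0 and d at T1, T2 and T3; two-sided test.

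**1. Group main effect.**
- Estimand: (0 + d + d + d)/4 = 0.75d.
- Variance of a person's four-visit mean: (1 + 3ρ)/4.
- At d = 0.25, ρ = 0.6: effect 0.1875, SE = √(0.70 × 4/164) = 0.131, ratio 1.43, power 0.30.
- At ρ = 0.75: SE = √(0.8125 × 4/164) = 0.141, ratio 1.33, power 0.26.

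**2. Group × time interaction (3 df).**
- The squared deviations of (0, d, d, d) from their mean sum to (0.75d)² + 3(0.25d)² = 0.75d².
- Noncentrality: (82/2) × 0.75d²/(1 − ρ).
- At d = 0.25, ρ = 0.6: 41 × 0.0469/0.4 = 4.8, power 0.42.
- At ρ = 0.75: 41 × 0.0469/0.25 = 7.7, power 0.63.

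**3. Mean of T1–T3 adjusted for T0.**
- Estimand: d.
- Residual variance: (1 + 2ρ)/3 − ρ².
- At d = 0.25, ρ = 0.6: 0.733 − 0.36 = 0.373, SE = √(0.373 × 4/164) = 0.095, ratio 2.62, power 0.75 (normal approximation).
- At ρ = 0.75: 0.833 − 0.5625 = 0.271, SE = 0.081, ratio 3.08, power 0.87.

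**Range, same 164 completers:**

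| ρ | d | Group effect | Interaction | Adjusted T1–T3 mean |
|---|---|---|---|---|
| 0.3 | 0.3 | 0.55 | 0.35 | 0.82 |
| 0.5 | 0.3 | 0.44 | 0.48 | 0.85 |
| 0.6 | 0.25 | 0.30 | 0.42 | 0.75 |
| 0.7 | 0.3 | 0.37 | 0.72 | 0.93 |
| 0.75 | 0.25 | 0.26 | 0.63 | 0.87 |
| 0.8 | 0.3 | 0.34 | 0.89 | 0.98 |
| 0.7 | 0.4 | 0.58 | 0.94 | 1.00 |
| 0.8 | 0.4 | 0.54 | 0.99 | 1.00 |

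If the effect halves by T3 (ρ = 0.7, d = 0.3), the three powers are 0.27, 0.68 and 0.82, so the ordering is unchanged.

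**Side check, SI only.** The share of the 12-month fall look-back that lies before T0 is (52 − w)/52 at week w. In the intervention group T1 falls at 12–16 weeks, giving 77% to 69%. T2 falls at 24–32 weeks, giving 54% to 38%. At T3 the window is the 52 weeks after T2, out of 76–84 weeks of diary, i.e. 62–68% of the period over which falls are counted as the primary outcome.

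**The case against.** The best defence is that the interaction is the natural treatment test in a design with a pre-allocation level. The protocol names it, and T0 does not dilute it as it does the group effect. That stands: the plan contains a valid test, and with a large effect and high correlation it loses little. If the effect were confined to one visit, the interaction would keep the same noncentrality (again 0.75d²) while the averaged difference would fall to d/3. What remains is that the protocol does not designate the interaction as the treatment test and that it is less powerful for a sustained effect.

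Four stronger readings are tempting, and the documents do not support them.
- **Everyone with a missed visit is dropped.** This is the usual default of a classical repeated-measures ANOVA. The article does not state it, and missing-data handling may be set out in an analysis plan that is not shown. Deletion alone costs about 4 to 8 points of power for the T1–T3 average at d up to 0.3.
- **About half the power is lost.** This fits the group effect at d around 0.3 or less, and the interaction at modest d and ρ. It fails for the interaction at ρ of 0.7 or more with d of 0.3 or more. No d, SD or ρ is given for SI or TUG.
- **A time effect will be claimed as benefit.** The text says only that significant effects are followed up with post-hoc tests, and the Discussion frames the expected benefit against the control group.
- **SI at T3 repeats the primary outcome.** It overlaps with it. The fall count is one of ten inputs, and its window covers only part of the diary period. This is a separate matter of how SI is built and does not touch TUG.

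**Conclusion.** The point holds as a defect in the stated model for secondary outcomes. T0 is an outcome level although it precedes allocation, its value is not used as a covariate, and the treatment contrast is not named. The dilution of the group main effect to 0.75d follows from the design whenever the effect is constant after baseline. The power cost rests on the assumptions above. At d = 0.25 the adjusted T1–T3 mean gains 33 points over the interaction at ρ = 0.6 and 24 points at ρ = 0.75; over the group effect it gains 45 and 61 points. At d = 0.4 with ρ of 0.7 or more, the gain over the interaction is 6 points or less. Most of this does not depend on missing visits, since all tests were compared on the same completers. The primary fall outcomes are unaffected.

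**What to change.** Model T1, T2 and T3 as outcomes, with the T0 value as covariate (or a constrained common baseline), group, visit, group × visit and centre. Include every participant with any post-baseline value. Prespecify the INT–CTR difference averaged over T1–T3 as the treatment test, with visit-specific contrasts as supportive. The average is the better choice for a sustained effect. With all available data (10/20/30% missing at T1/T2/T3, d = 0.25, ρ = 0.6), it has power 0.82, against 0.62 at T1 and 0.53 at T3 alone, or 0.51 and 0.42 if the level is split between those two. State that time main effects are not read as treatment effects.

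As an optional, separate sensitivity analysis for SI only, also report SI with the fall count held at its T0 value.

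The cost is a change of analysis wording. The optional analysis also needs SI recomputed from its stored inputs. No new data are collected.

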Based on this planning, we expect positive changes regarding the overall SI but also in the seven subsections (dimensions) addressing different risk factors for falls and for the timed up-and-go test. First positive results on risk factors can be expected after completing the first 24 training sessions using the hunova robot. After this period, an additional 24 training sessions lasting period of home-based training should sustain or even expand the positive changes in the following time. With 48 training sessions over at least 6 months, fall risk factors should positively be influenced in the participants. However, as primary outcomes, the number of falls and fallers within the training period and in a one-year follow-up period are the most relevant parameters. We believe that by applying our training programme, older adults having an increased fall risk (SI > 40%) can experience relevant improvements in functional performance, tested within different dimensions of fall risk, and a reduced number of falls and fallers as primary outcomes, compared to the control group.

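### Follow-up tests on SI and TUG use single-step Bonferroni; Holm's step-down keeps the same familywise error and never rejects less (cheap improvement, secondary outcomes only)

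*Protocol article*

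**What the plan says.** Protocol article, Planned statistical evaluation of outcomes: "Analyses of secondary outcomes (SI and TUG) will be based on 2 × 4 ANOVA / ANCOVA with groups (INT/CTR) and time of assessment" as factors, with covariates. The follow-up rule comes next: "Significant main or interaction effects will be investigated further using Bonferroni post-hoc-tests". The error level is given once: "The significance level is set to *p* < 0.05". The article does not list the follow-up contrasts or say how many there are.

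The primary outcomes are handled separately: "An analysis of primary outcomes (i.e., number of falls and number of persons who have fallen) will be based on binomial regression analyses". The Bonferroni sentence follows the ANOVA/ANCOVA and does not govern that analysis.

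Under Expected key results, the authors expect first gains on risk factors after the 24 robot sessions, and say that the home-based block "should sustain or even expand the positive changes in the following time".

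**The concern.** The article names a correction, so this is a choice it has made and not a detail left to an analysis plan. Single-step Bonferroni holds every contrast in the family to the strictest threshold, however many of the others have already been rejected. Holm relaxes the threshold after each rejection and needs no additional assumption.

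The difference matters most when several contrasts are truly non-null. That is the pattern the article predicts: a gain after the robot block that is kept or enlarged afterwards. What is at stake is the chance of showing that gain at each later visit on SI and TUG. No conclusion about falls is involved.

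**Working it through.** **No figure in the plan to reproduce.** The article states no power, effect size or sample size for SI or TUG. Its sample size rests on falls: "it is assumed that the intervention will reduce the number of falls by 23% in comparison to the control group", which "yielded a required total sample size of 181 persons". The check is therefore a comparison of two procedures under declared assumptions.

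**Inputs**
- Number per arm, derived from the article: "Assuming that the study will have an overall dropout rate of 30% [10], a total number of 235 participants to be included in the study". 235 × 0.70 = 164.5, and equal allocation gives about 82 per arm.
- Level 0.05 from the article; two-sided is assumed.
- Assumed: three INT–CTR contrasts (T1, T2, T3), normal test statistics with pairwise correlation 0.6, and a standardised difference d of 0.4 or 0.5 where an effect exists.

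**Rules for m = 3**
- Bonferroni: reject each contrast with p ≤ 0.05/3 = 0.0167.
- Holm: order the p-values and compare the smallest with 0.05/3 = 0.0167, the next with 0.05/2 = 0.025 and the largest with 0.05. Stop at the first failure.

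The first Holm step is the Bonferroni threshold. Two things follow without simulation: Holm rejects whatever Bonferroni rejects, and the chance of at least one rejection is identical.

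**Bonferroni power by formula.** Standard error of d: √(2/82) = 0.156. For d = 0.4 the expected z is 0.4/0.156 = 2.56. The two-sided critical value at 0.0167 is 2.394. Power ≈ Φ(2.56 − 2.394) = Φ(0.17) ≈ 57%.

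**Simulation** (400,000 draws per scenario, 82 per arm, correlation 0.6)

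| True d at T1 / T2 / T3 | Contrast | Bonferroni | Holm | At least one rejection (both) |
|---|---|---|---|---|
| 0.4 / 0.4 / 0.4 | each visit | 57% | 64% | 78% |
| 0.5 / 0.5 / 0.5 | each visit | 79% | 85% | 93% |
| 0.5 / 0.4 / 0.3 | T3 | 32% | 44% | 84% |
| 0.4 / 0.4 / 0 | each true visit | 57% | 60% | 72% |
| 0.4 / 0 / 0 | T1 | 57% | 57% | 58% |

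Power to reject at all three visits rises from 34% to 51% for d = 0.4, and from 62% to 77% for d = 0.5.

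**Error control.** With no true effect, the familywise error is 4.2% for both procedures. With one null contrast (0.4 / 0.4 / 0) it is 1.7% for Bonferroni and 3.3% for Holm. Holm uses error that Bonferroni leaves unspent and stays within 5%.

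**Sensitivity**
- d = 0.4 at all three visits, correlation 0.3: 57% against 65% per visit. Correlation 0.8: 57% against 63%.
- d = 0.4 at all three visits, 90 per arm (about half of 181), correlation 0.6: 61% against 69%.
- Four contrasts including a null one at T0, 90 per arm, d = 0.4 at the other three: 57% against 62%.

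The simulation leaves out the requirement of a significant main or interaction effect. That requirement applies equally under either correction, and it can only lower the absolute figures.

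**The case against.** The strongest reply is that nothing here is wrong. Bonferroni is prespecified, familiar and valid, and the article nowhere promises the most powerful correction or sets a power target for SI or TUG. This stands: the point is an improvement and not a fault.

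Second, the contrast family and effect sizes are assumed, and the larger gains need effects at all three visits. This also stands. With one true effect the gain vanishes. The all-three-visits figures answer a success criterion that the article does not set. The expectation of a sustained benefit makes the favourable case plausible, but it remains conditional.

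Third, Bonferroni has simple simultaneous confidence intervals that agree with its tests, and Holm does not. That is a real cost and a legitimate reason to prefer Bonferroni.

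Three stronger readings are tempting, and the document supports none of them:
- A reader might infer that Bonferroni could make a sustained benefit look as if it had faded. A non-significant visit is not evidence of fading under either method; estimates and intervals address that question.
- A reader might infer that the trial's main result is at risk. The primary outcomes are analysed by binomial regression, outside this sentence.
- A reader might attribute to the method the loss that a very large set of pairwise comparisons would bring. That loss comes from the size of the family, which the article does not state, and Holm would suffer most of it too.

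**Conclusion.** The point holds as an optional, low-cost improvement to the follow-up tests on two secondary outcomes. That Holm dominates Bonferroni at the same familywise 5% is a mathematical fact and needs none of the assumed inputs. The size of the gain does need them. With 82 per arm, three contrasts, correlation 0.6 and d = 0.4 where an effect exists, it is about 7 points per visit if all three visits have a true effect, about 3 if two do, and about 0 if one does. The chance of at least one significant visit, the analysis of falls and fallers, and the sample size of 235 are unaffected.

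**What to change.** In Planned statistical evaluation of outcomes, replace the Bonferroni wording by: *post-hoc tests with Holm's step-down adjustment at familywise 5%*. Keep the condition that a main or interaction effect is significant, and keep whatever family of contrasts is planned, so that only the adjustment changes. Report Bonferroni-adjusted confidence intervals beside the Holm-adjusted p-values, with a note that the two come from different procedures.

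The cost is one sentence, with no extra data. The downside is the occasional contrast where Holm rejects and the Bonferroni interval includes zero. Authors who want intervals and tests always to agree can reasonably keep Bonferroni, accepting the lower power shown above.

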## Discussion

### Expected key results

Important predictors of fall risk, such as muscle function, balance control and gait quality, can be improved by appropriate fall prevention interventions [10, 11]. Effective fall prevention strategies should simultaneously address different risk factors [10, 12, 13]. Exercise-based strategies are most effective when they combine balance exercises and functional exercises optionally supplemented with strength training [10].

Although several studies in recent years used miscellaneous new technology within novel fall prevention interventions [23–28], so far, the potential contribution of the hunova robot (Movendo Technology, Genoa, Italy) to reducing fall risk has not been investigated. Based on clinical studies that demonstrated positive results in the rehabilitation of stroke patients as well as in patients with Parkinson’s disease (PD) [37, 38]. Cella et al. [35] demonstrated that the hunova robot can discriminate and evaluate older patients and predict falls. Furthermore, the hunova assessment can discriminate older persons with different grades of impairment of physical performance [50]. With this in mind, the hunova robot seems to be suitable for fall prevention. With its specific assessment strategy which results in an individual fall risk score (SI) and the possibility to create an individually tailored specific exercise programme based on the deficits in the dimensions, the hunova robot provides a new approach to fall prevention. To ensure training success, basic principles of exercise / training science were considered within the training programme.

Based on this planning, we expect positive changes regarding the overall SI but also in the seven subsections (dimensions) addressing different risk factors for falls and for the timed up-and-go test. First positive results on risk factors can be expected after completing the first 24 training sessions using the hunova robot. After this period, an additional 24 training sessions lasting period of home-based training should sustain or even expand the positive changes in the following time. With 48 training sessions over at least 6 months, fall risk factors should positively be influenced in the participants. However, as primary outcomes, the number of falls and fallers within the training period and in a one-year follow-up period are the most relevant parameters. We believe that by applying our training programme, older adults having an increased fall risk (SI > 40%) can experience relevant improvements in functional performance, tested within different dimensions of fall risk, and a reduced number of falls and fallers as primary outcomes, compared to the control group.

### Benefits and risks

Participants who take part in the fall prevention training programme using the hunova robot and the subsequent home-based training programme have potential benefits from an individually tailored training programme that takes basic principles of exercise / training science into account. No adverse events are expected during the measurements or the intervention using the hunova robot and the first two training sessions of the home-based programme because of the supervision of trained sport or physio-therapists who are trained with all details of the training programme in advance. In addition, all training content is developed based on current knowledge of training science, e.g., having a progression over time, first balance exercises and strengthening exercises at the end. During the supervised training sessions, participants are always made aware of potential hazards and learn how to assist themselves, e.g., during balance exercises, or having problems within an exercise. In addition, different potential adjustments, and modifications to simplify and to complicate the exercises are given by the therapists. With this preparation over the first 26 training sessions (supervised by the therapists in the study centres: 24 sessions TSEP + 2 sessions HBEP = 26 sessions on-site), having the manual and the accompanying videos, participants should be optimally prepared for the home-based training programme in the second period. By implementing the health questionnaire and carefully selected inclusion and exclusion criteria, all participants are expected to fulfil the prerequisites for study participation. Measurements and training sessions are instructed and supervised by well-trained personnel, so that potential risks are minimised. Proper safety precautions additionally minimize the risk of uncomfortable and adverse events. In summary, the expected benefits exceed the potentially occurring risks.

